## Abstract

**Background:**

Venous leg ulcers (VLUs) are the commonest cause of leg ulceration, affecting 1 in 100 adults. There is a significant health burden associated with VLUs – it is estimated that the cost of treatment for 1 ulcer is up to £1300 per year in the NHS. The mainstay of treatment is with graduated compression bandaging; however, treatment is often prolonged and up to one quarter of venous leg ulcers do not heal despite standard care. Two previous trials have suggested that low-dose aspirin, as an adjunct to standard care, may hasten healing, but these trials were small and of poor quality. Aspirin is an inexpensive, widely used medication but its safety and efficacy in the treatment of VLUs remains to be established.

**Methods/Design:**

AVURT is a phase II randomised double blind, parallel-group, placebo-controlled efficacy trial. The primary objective is to examine whether aspirin, in addition to standard care, is effective in patients with chronic VLUs (i.e. over 6 weeks in duration or a history of VLU). Secondary objectives include feasibility and safety of aspirin in this population. A target of 100 participants, identified from community leg ulcer clinics and hospital clinics, will be randomised to receive either 300 mg of aspirin once daily or placebo. All participants will receive standard care with compression therapy. The primary outcome will be time to healing of the reference ulcer. Follow-up will occur for a maximum of 27 weeks. The primary analysis will use a Cox proportional hazards model to compare time to healing using the principles of intention-to-treat. Secondary outcomes will include ulcer size, pain evaluation, compliance and adverse events.

**Discussion:**

The AVURT trial will investigate the efficacy and safety of aspirin as a treatment for VLU and will inform on the feasibility of proceeding to a larger phase III study. This study will address the paucity of information currently available regarding aspirin therapy to treat VLU.

**Trial registration:**

The study is registered on a public database with clinicaltrials.gov (NCT02333123; registered on 5 November 2014).

**Electronic supplementary material:**

The online version of this article (doi:10.1186/s13063-015-1039-9) contains supplementary material, which is available to authorized users.

## Background

Venous leg ulcers (VLUs) are wounds of the lower limb caused by a diseased venous system, typically occurring in the gaiter area of the leg. VLUs represent the most common cause of leg ulceration, with a lifetime prevalence of 1–3 % in UK adults and accounting for around 85 % of all lower limb ulcers [1].

Many VLUs take over 6 months to heal; one large study demonstrated a median time to ulcer healing of 99 days with 2-layer compression therapy [2]. In addition, more than a quarter fail to heal completely [3] and the 12-month recurrence rate of healed VLUs may be up to 28 % [4, 5]. Patients with longstanding, large ulcers, or who have a prior history of ulceration, are particularly resistant to healing [6, 7]. VLUs impair quality of life (QoL); they are open wounds, which can be large, are often painful, frequently become infected and leak exudate. Compression bandaging is an effective treatment [8] but requires the use of sometimes bulky bandages alongside the need for regular clinic visits. Health-related QoL is decreased in patients with VLUs, which can incur significant psychological morbidity [9], and successful treatment has been shown to significantly improve QoL [10]. VLUs represent a significant health economic burden, costing up to £1300 to treat 1 VLU episode for a year in the UK [11]. There is, therefore, an unmet need for a more cost-effective and clinically effective treatment for VLUs.

### Pathophysiology of venous leg ulcers

In a healthy individual, flow of venous blood back to the heart occurs via the superficial venous system through the deep venous system, using the calf muscle pump and the venous valves to facilitate this flow against gravity. Resting hydrostatic venous pressure in the lower limb is 80 mmHg in the standing position, with no pressure gradient. When exercising, pressure in the deep venous system exceeds 80 mmHg, due to contraction of the calf muscles, forcing blood flow towards the heart. Valves in the superficial and perforator venous systems close to prevent retrograde flow. When the leg muscles relax again, pressure in the deep system falls below 80 mmHg, allowing blood to flow from the superficial system to the deep system through patent valves. Any dysfunction along this pathway may contribute to the development of venous ulceration.

VLUs most commonly result from impaired venous return due to calf muscle pump failure, usually as a result of obstruction or valve dysfunction in the superficial, deep or perforator venous system in the leg (primary venous disease). VLUs may also occur following a deep vein thrombosis or trauma (secondary venous disease). Other important factors include obesity and immobility.

Pathological maladaptation underlying VLUs include structural changes in vessel walls such as intimal hyperplasia, increased collagen content in areas of hypertrophy, as well as reduced smooth muscle cells and extracellular matrix [12]. These changes are likely triggered by inflammation and contribute to loss of venous tone and, ultimately, venous reflux and hypertension. These structural changes are also accompanied by cellular changes in the wound and wound bed – increased proteolytic activity, platelet aggregation and infiltration of leucocytes into the dermis, causing dermal fibrosis and leading to cutaneous changes such as lipodermatosclerosis, haemosiderin deposition and ulceration. Haemodynamic changes resulting from venous hypertension also affect the microcirculation, promoting interstitial oedema and capillary leakage. This combination of inflammatory activities may cause the VLU to heal slowly, or not at all. Targeting and reversing these pathophysiological pathways is the focus of adjunctive drug treatment.

### Current treatment of venous leg ulcers

Careful and regular clinical assessment should be the first step in the management of venous ulceration and should ideally be performed in a specialised venous ulcer clinic. All patients should have a venous Duplex scan to assess for treatable venous disease. Ulcer area and characteristics should be monitored over time, as the changing nature of an ulcer (depth, area, base, ulcer edge) can indicate progression of disease or healing. Bacteriological swabs and antibiotics should only be used in cases of proven clinical infection and a biopsy may be considered in cases of atypical or non-healing ulceration. Simple dressings, meticulous wound care and judicious sharp debridement should be undertaken by experienced practitioners. All patients with VLUs should have ankle brachial pressure index (ABPI) performed prior to the instigation of treatment to exclude arterial disease and should have cardiovascular risk factors addressed in the presence of an abnormal ABPI, in addition to referral to a vascular surgeon. Compression therapy should be instigated and undertaken by an appropriately trained professional. According to Scottish Intercollegiate Guidelines Network (SIGN) guidelines, patients with a chronic non-healing VLU and concomitant superficial venous reflux should be referred for consideration for surgery to prevent recurrence [13].

### Compression therapy

The standard treatment of VLUs is multi-layered compression bandaging (aiming for a pressure of 40 mmHg at the ankle [14] with the aim to reduce venous hypertension, improve calf muscle function and create a wound environment that encourages healing whilst reducing tissue maceration and excessive oedema and moisture. Compression is recommended as first-line treatment for VLUs in major UK guidelines [13].

The ‘gold standard’ is four-layer multi-component compression therapy [15]; however, this is often considered unsightly and uncomfortable due to the bulky nature of the bandages, and may restrict movement at the ankle, making it difficult to wear shoes. In addition, poor application technique may reduce the effectiveness of compression and the negative physical and social impact of compression stockings may lead to ambivalence about their effectiveness and subsequently lead to non-compliance [16]. Two-layer compression stockings are an alternative to four-layer bandaging and a recent randomised trial has demonstrated a reduction in ulcer recurrence with the two-layer approach [2, 17]. Various single-layer hosiery are also available; however, these do not meet the 40-mmHg targeted compression pressure.

### Topical therapy

Topical therapies have been used for VLUs (including silver-containing antibiotics, zinc oxide and other topical antimicrobials or impregnated dressings) although there is no reliable evidence to suggest that complex wound dressings are better than simple non-adherent dressings [18]. Topical local anaesthetic creams may help bring symptomatic relief when the ulcers are painful.

### Adjunctive drug treatment

Various drug adjuncts to compression have also been investigated, with a recent Cochrane Review demonstrating that pentoxyfilline (a vasodilator that decreases blood viscosity, modifies leucocyte activity and has some anti-platelet effects) is effective in improving wound healing when used with, and possibly without, four-layer compression [19]. However, vasodilators such as pentoxyfilline are not routinely prescribed in the National Health Service (NHS) and may produce intolerable adverse events (AEs), including potentially life-threatening side effects such as haematemesis, gastrointestinal haemorrhage and thrombocytopenia [20]. There is insufficient evidence to recommend the use of other adjunctive drugs, including venoactive drugs that increase venous tone via mechanisms that remain largely unclear.

### Aspirin

Aspirin is a cyclooxygenase inhibitor that irreversibly reduces prostaglandin-2 and thromboxane A2, which are involved in inflammation and platelet aggregation [21]. It is inexpensive, widely used and readily available. The mechanism by which aspirin may hasten healing of VLUs is unclear but may be associated with a reduction of inflammation, or its effect on the microvascular circulation, including platelet activation. In one study investigating the haemostatic effects of aspirin in patients with VLU, the investigators demonstrated that participants were found to have increased levels of fibrinogen and shortened coagulation rate, when compared to age-matched and sex-matched controls and that treatment with aspirin caused prolongation of the coagulation rate, which increased the rate of ulcer healing [22].

There have been 2 small randomised trials to date that have investigated the use of aspirin (300 mg) in VLUs; however, the quality of evidence presented was low and more robust studies are required to confirm their findings. An additional file outlines the previous studies investigating aspirin in VLUs (see Additional file 1).

The first study was carried out in 1994 and demonstrated that 38 % more patients healed in the treatment group (aspirin plus compression) than in the control group (placebo plus compression) [23]; however, no patients healed within 4 months in the control group, which is surprising, given that the median time to healing with compression alone is around 3 months [15]. Although it provides some limited data about the potential use of aspirin therapy, the sample size of only 20 patients is insufficient to draw meaningful conclusions. In addition, patients were only followed-up for 4 months.

Over a decade later, a Spanish group conducted a small randomised pilot trial (*n* = 51 patients) of aspirin and compression, demonstrating that aspirin reduced the average time to healing but did not influence the rate of healing and had no effect on the rate of ulcer recurrence. In addition, after multivariate analysis was performed, aspirin was not demonstrated to be an independent predictor of healing [24] with only initial ulcer size at study entry remaining independently associated with rate of healing. Moreover, no information was presented regarding the placebo and there is uncertainty around the effect estimates. The quality of evidence that aspirin hastens healing of VLUs is, therefore, low and needs addressing through more robust studies.

In addition to the Aspirin for Venous Ulcers: Randomised Trial (AVURT), there are two ongoing randomised trials investigating the use of aspirin in VLU. ASPiVLU (ASPirin in Venous Leg Ulcer healing, ACTRN12614000293662) will investigate the use of 300 mg aspirin, in addition to standard 3-layer compression therapy, with the primary endpoint as the time to complete ulcer healing at or before 12 weeks from randomisation. Aspirin4VLU (Low Dose Aspirin for Venous Leg Ulceration, NCT02158806) will investigate 150 mg aspirin, in addition to routine care, on time to complete healing of the reference ulcer. In addition to the trials reporting individually, data from AVURT, ASPiVLU and Aspirin4VLU will be combined in order to carry out an individual patient data (IPD) meta-analysis. Any other relevant trials such as the two earlier trials will also be considered for inclusion.

### Other options: surgery and minimally invasive intervention

Varicose vein surgery for VLUs has not been shown to influence the time to VLU healing; however, it may decrease the rate and severity of recurrence [4, 25],. Minimally invasive techniques such as radiofrequency ablation, foam sclerotherapy and endovascular laser ablation have largely replaced traditional open surgical techniques in the treatment of varicose veins, where possible. There have been no large-scale randomised trials investigating the superiority of one technique over another when treating VLUs, although recent studies suggest some benefit from radiofrequency ablation to assist VLU healing [26]. However, a large multi-centre randomised trial is currently underway (EVRA – Early Venous Reflux Ablation ulcer trial), aiming to assess the influence of early endovenous treatment of superficial venous reflux in patients with VLUs, compared to standard compression therapy (NIHR HTA 11/129/197; ISRCTN02335796).

### Other options: cell-based therapy, skin grafts and acellular products

Research on novel treatments with cell-based therapy is currently in progress, with promising results from phase II and phase III trials investigating the use of allogenic cells, either applied topically or via injection onto areas of ulceration [27, 28] as well as growth factors [29]. However, such therapies are expensive, may be associated with significant side effects and are unlikely to become widely available in the near future. Acellular products, such as porcine mucosa, have been trialled to assist VLU healing, with promising results noted in one study [30]. A recent Cochrane Review of skin grafting for VLU (including autografts, allografts, xenografts and bioengineered artificial skin grafts) demonstrated that bilayer tissue-engineered skin replacement, used with compression, was the only skin grafting technique that may increase the rate of VLU healing [31], but data are very limited in this area.

### The need for AVURT – a randomised, placebo-controlled efficacy study

Whilst there have been two small trials to date that have investigated the use of aspirin in the treatment of VLUs, the quality of the evidence presented is low. Given the significant health burden represented by VLUs, and the challenges in treating the disease, there is a need to identify effective, inexpensive, safe and widely available treatments that patients may tolerate. The AVURT seeks to investigate the effect of aspirin on time to healing of VLUs, to examine safety issues in this cohort of patients and to inform on the feasibility of proceeding from a phase II trial to an efficacy and effectiveness (phase III) trial. If a simple, cheap and well-tolerated medication, such as aspirin, were to result in a reduction in time to healing, this would impact on patient management, resource use and the potential impact on the population is substantial, given that aspirin is widely available. Meta-analyses have demonstrated that low-dose aspirin increases the risk of major bleeding compared to placebo [32, 33]; however, the absolute increase is modest and there is no evidence that decreasing the dose will reduce the risks of side effects [34]. The study will also provide the opportunity to systematically review the safety profile of aspirin in this population of patients, as well as assess the generalisability of the medication by studying the number of patients with VLUs who are currently taking aspirin or other anti-platelet medications.

## Methods/Design

### Trial design

The AVURT is designed to inform the feasibility of a larger, confirmatory study of aspirin therapy for VLU. AVURT is a phase II randomised, double blind, parallel-group, placebo-controlled study to provide evidence regarding the efficacy and safety of aspirin (at a dose of 300 mg once daily), in addition to standard care in patients with chronic VLUs. A chronic VLU is defined as any break in the skin that has either: a) been present for more than 6 weeks, or b) occurred in a person with a history of venous leg ulceration. Ulcers will be considered venous if no other aetiology is clinically suspected. The ulcer must be venous in appearance (i.e. moist, shallow and irregular of appearance) and lie wholly or partially within the gaiter area of the leg. Potential participants will be identified from hospital outpatient clinics or community leg ulcer clinics, where they usually receive treatment for VLUs. An additional file shows the schematic of the AVURT trial design (see Additional file 2). All participants will continue to receive ‘standard care’ according to an evidence-based standardised approach to the management of VLUs, as per SIGN guidelines [13] with multi-component compression therapy aiming to deliver 40 mmHg of pressure at the ankle. The type of dressing used will be at the discretion of the healthcare professional managing the patient and will be documented in the participant case report form (CRF).

Aspirin will be provided as a 300-mg capsule identical in weight, colour and size to the matched placebo capsules. Placebo capsules will contain a lactose and magnesium stearate blend. Capsules will be packaged into child-resistant tamper evident bottles sufficient in size to hold 190 doses for the participant to complete 24 weeks treatment.

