### Randomisation and blinding

Participants will be randomised on a 1:1 basis to receive either aspirin (300 mg) or placebo, in addition to standard care. The Research Pharmacy responsible for dispensing all trial medication (St George’s Hospital) will receive a randomisation schedule generated in advance by the IMP manufacturer, Sharp Clinical Services UK Ltd. (Sharp Clinical Services, UK) Stratification will be by ulcer size (≤5 cm^2^ or > 5 cm^2^).

Randomisation will be performed by the Research Pharmacy upon receipt of a valid prescription for a participant. Researchers, treating staff, clinicians and participants will be blind to treatment allocation. A 24-hour code-breaking service will be provided by the Research Pharmacy in case of requirement for emergency unblinding and participants will receive a study-specific 24-hour emergency contact card.

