#### Primary outcome analyses

Time to ulcer healing will be presented by trial arm using a Kaplan-Meier plot and a log-rank survival comparison will be made. The median time to healing will be presented overall and by trial arm with corresponding 95 % CIs. The primary analysis will investigate differences between trial arms in relation to time to ulcer healing using a Cox proportional hazards regression model. Adjustments will be made for log transformed area and duration of the reference ulcer. The model will be tested for inclusion of shared centre frailty effects.

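### Prior ulceration, which the protocol calls prognostic and uses as an entry route, is left out of the primary Cox model; adding it is a minor, nearly free improvement

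*Protocol article*

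**What the plan says.** Under Trial design, the protocol defines a chronic ulcer as one that has "been present for more than 6 weeks, or b) occurred in a person with a history of venous leg ulceration". An ulcer of 6 weeks or less can therefore enter only through the patient's history.

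The Background states the prognostic view: "Patients with longstanding, large ulcers, or who have a prior history of ulceration, are particularly resistant to healing". That names three features: duration, size and prior history.

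The design and analysis use two of them. Under Randomisation and blinding, "Stratification will be by ulcer size", with a single cut at 5 cm². Under Primary outcome analyses, "Adjustments will be made for log transformed area and duration of the reference ulcer", and a shared centre frailty is to be tested. Prior history is in neither place. The adjustment set matches the one behind the assumed standard error in the Sample size calculation (log area and log duration, taken from an earlier trial).

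**The concern.** The protocol makes a prognostic statement about three features and then carries only two into the primary model. The third is one that sites must ask about to apply the second entry route, so for some participants it is already elicited. The protocol states the adjustment set outright, so this is a choice the document makes and not a detail deferred to the analysis plan.

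What is at stake is efficiency and protection against chance imbalance. Both count for something here because the protocol expects a borderline result: at a hazard ratio of 1.5 its own interval just includes 1. With about 50 participants per arm, a binary factor that is not balanced by design can easily differ by several percentage points.

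**Working it through.** **Inputs from the protocol.** Total 100, allocated 1:1; hazard ratio about 1.5; standard error of the log hazard ratio 0.22; stated interval (0.97, 2.31); 25 weeks (175 days) of follow-up; a 99-day median healing time from one large study cited in the Background.

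**Inputs that are assumptions.** The documents give neither the prevalence of prior ulceration nor its effect. The ranges used are a prevalence of 30% to 70% and a healing-rate ratio for prior history of 0.7 to 0.5.

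**1. The plan's own figure.** 1.96 × 0.22 = 0.431, and exp(0.405 ± 0.431) = (0.97, 2.31). It reproduces. The printed half-width of 0.435 would give an upper limit of 2.32, a rounding matter. The calculation makes no use of prior history.

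**2. Size of chance imbalance.** With 50 per arm, the SD of the difference in proportions is √(2p(1−p)/50). This is 0.092 at p = 0.3 or 0.7, and 0.100 at p = 0.5. A difference of at least 10 points, in either direction, has a probability of about 28% to 32%; one of at least 20 points, about 3% to 5%.

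**3. Effect of an imbalance on the log hazard ratio (approximate).** The shift is imbalance × |ln(history ratio)|.
- 10 points: 0.1 × |ln 0.7| = 0.036; 0.1 × |ln 0.5| = 0.069.
- 20 points: 0.071 and 0.139.

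A 10-point imbalance is thus 0.036/0.22 = 0.16 to 0.069/0.22 = 0.32 of a standard error. The planned lower limit is 0.405 − 0.431 = −0.026 on the log scale. A shift of 0.036 in aspirin's favour would take it to +0.010, just above a hazard ratio of 1; the same shift the other way would take it to −0.062.

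**4. Cox model with and without history.** 1,000 simulated trials per scenario, N = 100, exponential healing times, 99-day median, censoring at 175 days, entry rule as written, 60% prevalence of history. Both models contain log area (generating coefficient −0.4) and log duration (−0.3). There were about 69 to 75 healing events per trial.

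| True HR | History ratio | Mean HR without → with | Mean SE without → with | Rejection without → with |
|---|---|---|---|---|
| 1.5 | 0.7 | 1.497 → 1.511 | 0.239 → 0.241 | 39.8% → 40.4% |
| 1.5 | 0.5 | 1.487 → 1.525 | 0.239 → 0.242 | 38.1% → 41.8% |
| 1.0 | 0.7 | 0.996 → 0.996 | 0.246 → 0.248 | 6.6% → 7.0% |
| 1.0 | 0.5 | 1.006 → 1.007 | 0.247 → 0.249 | 4.4% → 4.9% |

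Omitting history leaves the null estimate at 1. The null rejection rates scatter around 5% (simulation error about ±1.4 points). The 6.6% is slightly outside that band, but the model with history gave 7.0% in the same replicates, so the omission is not the cause; a separate null run with history omitted gave 5.1%.

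Under a true effect the estimate is attenuated by 1 − 1.497/1.511 = 0.9% to 1 − 1.487/1.525 = 2.5%. In a Cox model the loss shows up as this attenuation and not as a larger standard error. The ratio of mean log HR to SE rises from 0.404/0.239 = 1.69 to 0.413/0.241 = 1.71, and from 0.397/0.239 = 1.66 to 0.422/0.242 = 1.74.

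**5. Does the entry rule matter?** A second simulation (3,000 trials per scenario, history in half of candidates, true HR 1.5) was run with the rule as written, and again with the same marginal distributions but history independent of duration.

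| History ratio | Entry rule | Mean log HR without → with | Power without → with |
|---|---|---|---|
| 0.5 | as written | 0.396 → 0.423 | 37% → 41% |
| 0.5 | link removed | 0.386 → 0.413 | 36% → 41% |
| 0.7 | as written | 0.410 → 0.418 | 41% → 42% |
| 0.7 | link removed | 0.412 → 0.421 | 41% → 41% |

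The gain in log HR from adding history is 0.027 with the rule and 0.027 without it at a ratio of 0.5, and 0.008 and 0.009 at 0.7. What the rule changes is the duration coefficient when history is left out: about −0.23 with the rule and −0.29 without it.

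**The case against.** The strongest case against has four parts.

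- **Validity is not in question.** Randomisation protects the comparison whether or not a prognostic covariate is modelled. An imbalance of the size in step 3 is part of the sampling variation that the standard error already describes, and the argument applies to any unadjusted covariate. This stands. It limits the point to efficiency and to conditioning on an imbalance that is actually observed.
- **The protocol contains contrary evidence.** Of the earlier 51-patient aspirin pilot it reports a multivariate analysis "with only initial ulcer size at study entry remaining independently associated with rate of healing". The Background also does not claim that history predicts healing independently of size and duration. This stands in part: the benefit may be nil. But the protocol grades that evidence as low quality, and the same reasoning would remove duration, which the protocol keeps.
- **The covariate set is deliberate.** It matches the set behind the assumed standard error and suits a later individual patient data meta-analysis. This is a reason to retain the two-covariate model, which a sensitivity analysis does.
- **The article may not show everything.** Prior history may be on the baseline form, and the analysis plan may already add it. This is possible, and a reader should not infer that history goes unrecorded.

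A stronger reading is tempting: that the two-route entry rule corrupts the duration adjustment, gives it the wrong sign and so pulls the treatment effect towards 1. This is not supported. In simulation the duration coefficient stays negative (−0.23 to −0.27, against −0.31 with history in the model), so it is attenuated and not reversed. It is a nuisance parameter, and step 5 shows the same treatment-effect attenuation once the link between history and duration is removed.

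**Conclusion.** The point holds as a minor one. The protocol calls prior ulceration prognostic and uses it for entry, but adjusts for only two of its three named features. This is not an error, a contradiction or a threat to validity: there is no bias under the null, and type I error is unaffected.

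The cost is an attenuation of the hazard ratio of about 1% to 2.5%, a power loss of about 0 to 5 points, and exposure to a shift of about 0.04 to 0.07 in the log hazard ratio from a 10-point imbalance. All of these assume a healing-rate ratio for prior history between 0.7 and 0.5, at the assumed prevalences. The documents supply neither figure, and absolute power in the simulations depends on the assumed event rates; the differences between models are what count.

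A reader might also conclude that history should have been a stratification factor. Nothing here supports that: with 100 participants, stratifying by size alone is defensible, and covariate adjustment achieves what is needed.

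**What to change.** Record history of venous leg ulceration (yes/no) at baseline for every participant, not only those who qualify through it. Pre-specify it in the analysis plan, before any data are analysed, as a covariate in the primary Cox model alongside log area and log duration. Keep the two-covariate model as a sensitivity analysis, for comparability with the earlier trial that supplied the standard error and with the planned meta-analysis. Tabulate prior history by arm.

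The cost is one baseline item, which sites must already ask about to apply the second entry route, and one degree of freedom against about 70 to 75 expected healing events. If history has no effect, practically nothing is lost: simulated power for the two models was 41.0% and 40.8%. Stratification, sample size and clinical procedures are unchanged.
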